## Abstract

**Introduction:**

Modern medical treatment of insomnia is often associated with issues like addiction, drug resistance, and a high risk of relapse post drug withdrawal. To tackle these challenges, the Chinese medicine formula Shuhe granule (SHG) has been employed in insomnia treatment at Guangdong Provincial Hospital of Chinese Medicine. Despite this, there is currently a lack of reliable evidence from evidence-based trials to support the widespread use of SHG in insomnia treatment. Therefore, we have developed a randomized controlled trial to assess the efficacy and safety of SHG in insomnia treatment.

**Method:**

This study will be a single-center, double-blind, randomized, parallel group, placebo-controlled clinical trial involving a total of 160 eligible patients aged between 18 and 65. Participants will be randomly assigned to either the intervention group, receiving SHG, or the placebo group receiving placebo granules. Follow-up visits will occur every 2 weeks from baseline to 2 months. The primary outcome is the perceived insomnia severity measured by the Insomnia Severity Index. The secondary outcome measures include the Pittsburgh Sleep Quality Index, Fatigue Severity Scale, Patient Health Questionnaire, Generalized Anxiety Disorder, Visual Fatigue Analogue Scale, Traditional Chinese medicine syndrome score, and Polysomnography.

**Discussion:**

The results of the study are expected to provide evidence of high methodological and reporting quality on the efficacy and safety of SHG for insomnia.

**Trial Registration Numbers:**

http://itmctr.ccebtcm.org.cn/, ITMCTR2024000035.

## 1 Introduction

Currently, chronic insomnia is emerging as a global epidemic with a significant increase in prevalence in China. Epidemiological surveys have shown that insomnia affects 29.2% of the general population (Shi et al., 2020) and 38.9% of medical staff (Pappa et al., 2020). The consequences of chronic insomnia go beyond sleep disturbances, impacting various aspects of health including physiological, psychological, and cognitive functions. Patients with insomnia experience disrupted sleep patterns leading to reduced sleep quality, impaired daytime functioning, and potential development of mental health issues such as anxiety and depression (Hertenstein et al., 2019; Riemann, 2022; Scott et al., 2021). Moreover, chronic insomnia is linked to compromised immune function, heightened risk of cardiovascular diseases, metabolic imbalances, and increased sensitivity to pain (Yin et al., 2017; Sanjari Moghaddam et al., 2021).

Sleeping pills are commonly used to treat insomnia clinically. While they can provided short-term relief from sleep deprivation, they may also lead to issues like abuse and addiction (Hajak et al., 2003). Chronic insomnia patients using sleeping pills long-term often experience adverse reactions, withdrawal symptoms, and rebound insomnia (Wilt et al., 2016). Moreover, the long-term effects of these medications may be uncertain due to the higher risk of side effects (Wilt et al., 2016). Therefore, apart from traditional treatments, exploring alternative safe and effective treatments for chronic insomnia patients is crucial.

In Traditional Chinese Medicine (TCM), it is believed that good health comes from the balance of Yin and Yang in the body, whereas disease is caused by an excess or deficiency of Yin or Yang, which is referred to as “Yin-Yang disharmony” (Hu et al., 2019). TCM theory posits that sleep is a result of the harmony between Yin and Yang, with Yang entering Yin leading to sleep and Yang exiting Yin leading to wakefulness. It asserts that the root cause of insomnia is often a disharmony between Yin and Yang, particularly an excess of Yang coupled with a deficiency of Yin. In TCM, there is a theory of Zang-Fu organs characterized five Zang organs which comprise solid organs such as the Heart, Spleen, Lung, Kidney, and Liver. Qi and Blood flow between Zang-Fu organs. TCM theory believes that Qi, Blood and Zang-Fu organs are the important material basis of the human body. Therefore, imbalance of qi and blood in the organs is also a key factor causing disease in traditional Chinese medicine. Previous studies have indicated that individuals with chronic insomnia may experience deficiencies in heart and kidney function, as well as imbalances in Qi and Blood due to the prolonged duration of the condition. The pathogenesis has evolved from “Yin-Yang disharmony, Yang exuberance with Yin debilitation” to “deficiency Yang floating upward”. Consequently, the treatment of chronic insomnia necessitates the warming and descending of Yang.

Based on this theory, Shuhe Granules (SHG), a representative Chinese patent medicine, was developed from the extensive clinical expertise of the renowned TCM physician [name]. It is an herbal formula comprising of nine medicinal herbs (Table 1). The chemical fingerprint analysis of SHG was performed using ultra-performance liquid chromatography coupled with Q-exactive Orbitrap mass spectrometry, revealing over 100 common chemicals peaks (Supplementary Material 1–5).

**TABLE 1 T1:** The components of the Chinese herbal formula Shuhe.

Herbal name	Dosage (g)	Produced from
*Cinnamomum cassia* (L.) J.Presl [Lauraceae]	15	Dried twig
*Paeonia lactiflora* Pall. [Paeoniaceae]	15	Dried root
*Glycyrrhiza uralensis* Fisch. [Fabaceae]	12	Dried root and rhizome
*Zingiber officinale* Roscoe [Zingiberaceae]	18	Fresh rhizome
*Ziziphus jujuba* Mill. [Rhamnaceae]	18	Dried fruit
*Panax ginseng* C. A. Mey. [Araliaceae]	10	Dried root and rhizome
*Angelica sinensis* (Oliv.) Diels [Apiaceae]	10	Dried root
*Ophiopogon japonicus (Thunb.) Ker Gawl*. [Asparagaceae]	10	Dried root
*Morinda officinalis* How [Rubiaceae]	10	Dried root

Our early single-arm pilot RCT of 62 participants showed that following a 2-week of SHG intervention, the Insomnia Severity Index (ISI) decreased by 15.38%, resulting in an average score reduction of 4.42 points. Additionally, the Pittsburgh Sleep Quality Index (PSQI) decreased by 16.23%, with an average score reduction of 2.63 points. Our findings suggest that ISI may be a more reliable indicator of the effectiveness of SHG compared to PSQI. No adverse events (AEs) were reported. However, there is currently insufficient evidence from evidence-based trials to support the widespread use of SHG for treating insomnia. As a result, we are planning to conduct a well-designed, randomized double-blind controlled clinical trial to further investigate the efficacy and safety of SHG in the treatment of chronic insomnia.

## 2 Methods

### 2.1 Investigational medications

Receive each qualified traditional Chinese medicine piece according to the prescription amount, add it to the extraction tank with drinking water, heat and decoct for extraction twice. For the first time, add drinking water 10 times the amount of the total medicinal materials, heat and extract for 1.5 h. For the second time, add drinking water 8 times the amount of the total medicinal materials, heat and extract for 1 h, combine the secondary filtrate and collect it in a settling tank for later use. This extraction ratio and time has been verified by the best process conditions of Shuxin Anshen Paste (SAP) in the early stage of our team research, and retains the effective ingredients of each herbal medicine to the greatest extent (Ting-yuan, 2024). SHG is modified from SAP, so we retain this extraction ratio. Extract the mixed filtrate in the settling tank to a vacuum concentrator for concentration, decompress it to a relative density of 1.030 ∼ 1.070 (measured at 60°C), collect and put it into a cold storage for later use. In addition, take maltodextrin, add 2–3 times of 80°C ∼ 100°C purified water, stir until completely dissolved, filter with 100 mesh sieve, add it to the qualified extract and mix evenly, heat the prepared mixed dip to 60 ∼ 70°C, spare. Take the above mixed extract, filter it through 100 mesh sieve, place it in a spray dryer and perform a spray drying operation to dry it to a moisture content of 5.0% (quick), collect it and set aside. Take Shuhe granules and spray dry powder and maltodextrin into a three-dimensional motion mixer and mix for 5–10 min to make them uniform. Take the mixed powder and place it in a dry granulator for granulation, pass it through a 14-mesh sieve, and use a 10-mesh/60-mesh vortex vibrating sieve to grind the dry granules. If the powder is qualified, collect it. Last, take the sieved particles and mix at 30 Hz for 3–5 min, collect and set aside.

“Type A extract” are botanical drugs, and their extracts are included in the national or regional pharmacopoeia used as active ingredients in phytopharmaceuticals with regulated medical use (licensed, listed, or registered medicines) (Heinrich et al., 2022). As a Type A extract, SHG is composed of 13 botanical drugs and functions to reconcile Qi and blood, warm and tonify the heart and kidney. Through modern pharmaceutical technology, the decoctions of SHG are then extracted, concentrated, dried, and shaped into granules. The quality control analysis of SHG used ultra-performance liquid chromatography (UPLC) (Heinrich et al., 2020). The daily dosage of SHG is as follows: Neolitsea cassia (L.) Kosterm. [Lauraceae; Guizhi-branch]: 15 g; Paeonia lactiflora Pall. [Paeoniaceae; Baishao-radix]: 15 g; *Zingiber officinale* Roscoe [Zingiberaceae; Shengjiang-rhizome]: 18 g; Glycyrrhiza uralensis Fisch. [Fabaceae; Gancao-radix et rhizome]: 12 g; *Ziziphus jujuba* Mill. [Rhamnaceae; Dazao-fructus]: 18 g; *Panax ginseng* C. A. Mey. [Araliaceae; Renshen-radix et rhizome]: 10 g; *Angelica sinensis* (Oliv.) Diels [Apiaceae; Danggui-radix]: 10 g; *Ophiopogon japonicus (Thunb.) Ker Gawl*. [Asparagaceae; Maidong-radix]: 10 g; *Morinda officinalis* How [Rubiaceae; Bajitian- radix]: 10 g.

### 2.2 Trial design

This is a single-center, randomized, double-blind, parallel group, placebo-controlled clinical trial. The trial will be conducted in the Guangdong Provincial Hospital of TCM. A total of 160 eligible participants will be randomized into the experimental group (SHG) or the control group (placebo) with a 1: 1 ratio. The duration of the intervention is 4 weeks and the total observation follow-up period will be 8 weeks. Study visits will take place at baseline and at 2, 4, 6, 8 weeks. Each patient will be asked to visit within 3 days of the given time point. All participants will be required to sign the written informed consent (Supplementary Material 6, 7) before randomization. This protocol was compiled in line with the Standard Protocol Items: Recommendations for Interventional Trials (SPIRIT) Guidelines (Supplementary Material 8; Chan et al., 2013). The flowchart of this trial is presented in Figure 1. The schedule of enrollment, interventions, and assessments is as shown in Table 2.

**FIGURE 1 F1:**
[figure not shown]
Study flowchart. SHG, Shuhe Granule; ISI, Insomnia Severity Index; PSQI, Pittsburgh Sleep Quality Index; FSS, Fatigue severity scale; PHQ-9, Patient Health Questionnaire; GAD-7, Generalized Anxiety Disorder; PSG, Polysomnography.

**TABLE 2 T2:** A standard protocol items: recommendation for interventions for trials (SPIRIT).

Study phase time	Baseline	Intervention period		Follow up	
	−1∼0 weeks	2 weeks	4 weeks	6 weeks	8 weeks
Data collection at baseline					
Eligibility screen	√				
Informed consent	√				
Demographic data	√				
Allocation	√				
Medical history	√				
Outcome measurements					
ISI	√	√	√	√	√
PSQI	√		√		√
FSS	√		√		√
GAD-7	√		√		√
PHQ-9	√		√		√
PSG	√		√		
Safety evaluation					
Blood routine	√		√		
Urine routine	√		√		
Liver and kidney function	√		√		
Electrocardiogram	√		√		
AEs		√	√	√	√

ISI, Insomnia Severity Index; PSQI, Pittsburgh Sleep Quality Index; FSS, Fatigue severity scale; PHQ-9, Patient Health Questionnaire; GAD-7, Generalized Anxiety Disorder; PSG, Polysomnography; AEs, adverse events.

“√” Represents the need for implementation at this point in time.

### 2.3 Setting

This study is being conducted in the Treatment and Prevention Center of Guangdong Provincial Hospital of Chinese Medicine. 160 participants will be recruited via putting up posters in the hospital areas. A specialist will be responsible for screening participants and assessing whether they meet with the inclusion criteria. A research assistant will provide the participants with the informed consent form.

### 2.4 Participants

#### 2.4.1 Diagnostic criteria for insomnia

According to the diagnostic criteria for chronic insomnia proposed by American Academy of Sleep Medicine in 2014, participants must meet all items A to F to be included in the study (Sateia, 2014). In accordance with the classification criteria of insomnia proposed by Charles M. Morin in 1993, 8≤ISI≤14, 15≤ISI≤21 and 22≤ISI≤28 represent mild, moderate, and severe insomnia. Only patients with mild to moderate insomnia were included in the study.

#### 2.4.2 Diagnostic criteria for “deficiency of heart and kidney, disorder of qi and blood syndrome” syndrome

Patients have two of the primary symptoms, and more than two of the secondary symptoms, indispensable tongue and pulse listed in the following to be diagnosed with the deficiency of heart and kidney, disorder of qi and blood syndrome (Table 3). Syndrome differentiation will be independently determined by two qualified researchers.(1) Primary signs and symptoms: insomnia, fatigue.(2) Secondary signs and symptoms: fear of cold and wind, cold limbs, palpitations, dizziness, spontaneous sweating, scant menstruation, pale lower eyelids or slightly red.(3) Tongue and pulse: pale red tongue, weak pulse, fine pulse and sunken pulse.

**TABLE 3 T3:** Diagnostic criteria for traditional Chinese medicine syndromes.

Deficiency of heart and kidney, disorder of qi and blood syndrome	
Primary signs and symptoms	1.Insomnia
	2.Fatigue
	The included patients need to have two of the above symptoms
Secondary signs and symptoms	1. Fear of cold and wind
	2. Cold limbs
	3. Palpitations
	4. Dizziness
	5. Spontaneous sweating
	6. Scant menstruation
	7. Pale lower eyelids or slightly red
	The included patients need to have two or more of the above symptoms
Tongue and pulse	1. Pale red tongue
	2. Weak pulse, fine pulse or sunken pulse
	The included patients need to have two of the above symptoms

#### 2.4.3 Inclusion criteria

Participants meeting the following criteria will be included:(1) The men and women patients are aged 18–65 years.(2) Patients who meet the diagnostic criteria for insomnia based on the International Classification of Diseases 11th Revision (Harrison et al., 2021).(3) Patients who meet the diagnostic criteria of insomnia in traditional Chinese medicine.(4) Patients who meet the deficiency of heart and kidney, disorder of qi and blood syndrome.(5) Patients who volunteer to participate in the trial and sign the informed consent form.

#### 2.4.4 Exclusion criteria

Participants with any of the following criteria will be excluded:(1) Meet two of the excluded symptomsa. Red lower eyelids.b. Feverish hands.c. Dry and hard stool.d. Thick and slimy fur or dry and coarse fur.e. The pulse-to-respiration ratio is greater than 5.3.(2) Patients who are pregnant, lactating, or plan to become pregnant, and with known mental disorders.(3) Based on the medical history and consultation, the doctor confirmed that secondary insomnia was caused by other diseases. For example, local pain, restless legs syndrome, sleep apnea syndrome (apnea-hypopnea index, AHI >15/h), acute or chronic heart failure, chronic obstructive pulmonary disease, acute or chronic bronchitis, etc.(4) Patients with severe depression [Patient Health Questionnaire 9 (PHQ-9) ≥ 15 score].(5) Patients with severe anxiety [Generalized Anxiety Disorder 7 (GAD-7) ≥ 15 score].(6) Patients with severe insomnia [Insomnia Severity Index (ISI) ≥ 22 score].(7) Patients participating in other clinical trials within 4 weeks of the screening period.(8) Patients with hemoglobin level less than 90 g/L, white blood cell counts less than 3.0 × 10^9^/L, or platelet count less than 100 × 10^9^/L.(9) Patients with glomerular filtration rate lower than 40 mL/min.(10) Aspartate aminotransferase (AST) or Alanine aminotransferase (ALT) levels greater than 1.5 times the upper limit of the normal range.(11) Patients who are allergic to the trial drug.

#### 2.4.5 Withdrawal/termination criteria

Participants will be withdrawn or terminated from the trial if they meet any of the following criteria:(1). Serious adverse events are reported at any time, and patients are unable to continue.(2). Patients who present with serious changes or complications related to the disease during the trial.(3). Patients who cannot comply with the instructions and follow-up procedures of this trial, leading to incomplete medical administration records, or patients who took banned drugs or other medications that may interfere with the efficacy and safety evaluation of this study.(4). Patients who request to be withdrawn from the trial.

Besides, researchers will record the last time of drug intake and collect evaluation items of participants who discontinue or deviate from intervention protocols.

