#### 2.7.2 Control group

Patients in the control group will receive placebo granules (2 bags at 15 mg each, orally, twice a day, with warm water) for 4 weeks, and the total observation follow-up period will be 8 weeks. In addition, counseling will be provided by research staff about management in insomnia.

If the participants’ condition has not improved during the clinical trial, the life and work are affected, or emotional changes, we will maintain a good communication with the patients, and give the temporary western medicine temporarily with the consent of fully knowledge. We will instruct patients on how to take medication and what precautions to take, and make a registration for taking medication. Observation for 1 week, during the medication, we will still to observe the changes in the condition at any time, and fall off when necessary. If the ISI remains unchanged or increased, but the GAD-7 and PHQ-9 scores increase ≤4 points, Stilnox 10 mg will be administered on an as-needed basis. Conversely, if the GAD-7 or PHQ-9 scores increase by ≥5 points, or if the anxiety and depression factor scores on the Symptom Checklist-90 are severe, Lorazepam 1 mg will be administered on an as-needed basis.

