An ITT analysis will be conducted utilizing the imputation method to address missing data. It is anticipated that the proportion of missing data points will be less than 20%. The linear trend at point method will be employed to substitute missing values. In this approach, the existing data series will be regressed against an index variable that is scaled from 1 to n, allowing for the replacement of missing values with their corresponding predicted values. In instances where predicted values cannot be determined, the last observation carried forward (LOCF) method will be implemented. Additionally, a sensitivity analysis will be performed without imputation to evaluate the robustness of the findings.

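### The withdrawal rule and the rescue-medication rule can treat the same patient differently, and the plan does not say whether ISI is still collected to week 4 after withdrawal

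*Protocol article*

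**What the plan says.** Four places in the protocol article bear on this point.

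- **Section 2.4.5, the rule.** "Participants will be withdrawn or terminated from the trial if they meet any of the following criteria". Criterion (3) has two limbs: "Patients who cannot comply with the instructions and follow-up procedures of this trial, leading to incomplete medical administration records", and "patients who took banned drugs or other medications that may interfere with the efficacy and safety evaluation of this study". Criterion (4) is the patient's own request. All four criteria have the same consequence. Stopping study drug is not separated from stopping follow-up.
- **Section 2.4.5, closing sentence.** "researchers will record the last time of drug intake and collect evaluation items of participants who discontinue or deviate from intervention protocols". It names no items and no visit.
- **Section 2.7.2.** Temporary western medicine may be given to patients who have not improved. One trigger begins: "If the ISI remains unchanged or increased, but the GAD-7 and PHQ-9 scores increase ≤4 points". The use is registered, and "we will still to observe the changes in the condition at any time, and fall off when necessary". I read the last words as dropping out where needed. The text stands under the control-group heading but speaks of participants generally; I take it to cover both arms, as the trial is double-blind.
- **Sections 2.8.1 and 2.11.** The primary outcome is the change in ISI after 4 weeks, analysed on the full analysis population under the ITT principle. For gaps, "The linear trend at point method will be employed to substitute missing values", with LOCF where no prediction is possible and a sensitivity analysis without imputation.

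**The concern.** An ITT comparison at week 4 needs the week-4 ISI of patients who stopped treatment or took something else. Section 2.4.5 can be read as ending their participation before that visit. The patients affected are not a random subset: section 2.7.2 ties rescue to the course of the ISI itself, and a hypnotic or anxiolytic is plausibly a medication that interferes with the efficacy evaluation. A rule in the plan could then remove patients because of the primary outcome, and their week-4 values would be filled by methods that take no account of why they are missing.

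**Working it through.** **1. The plan's own figure.** Section 2.10 inflates 128 evaluable patients for 20% loss: 128 / (1 - 0.20) = 160, as stated. The allowance is 160 - 128 = 32 patients. It covers loss of every kind, and nothing in the article says how many would come from section 2.4.5.

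**2. One patient followed through the sections.** ISI is scheduled at baseline and weeks 2, 4, 6 and 8. Take a patient whose week-2 ISI equals baseline and who receives rescue.

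- Under 2.7.2 the patient is observed further and drops out only where needed.
- Under criterion (3) of 2.4.5 the patient has taken a medication that may interfere with evaluation and is withdrawn from the trial. The criterion makes no exception for rescue given under the protocol.
- Under the closing sentence of 2.4.5 some assessment is made. It could be one exit visit at week 2 or all remaining visits.
- Under 2.11 the week-4 value is used if observed and filled if not.

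Whether this patient has an observed primary outcome depends on which reading the site adopts.

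**3. What imputation would supply.** The article does not say whether the index from 1 to n runs over patients or over one patient's visits.

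- *Over patients:* the filled value lies near the mean of all observed week-4 values, both arms pooled. With a fraction p missing in each arm, the filled patients contribute almost no difference between arms, so the estimate is about (1 - p) x the difference among completers.
- *Over visits at index 1, 2, 3:* the filled value is 2 x (week 2) - (baseline). With week 2 equal to baseline, the filled change is 0. LOCF gives the same here.

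Neither uses the reason for withdrawal.

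**4. Illustration. All inputs are assumed; none is in the article.** 80 per arm; mean ISI 16 at baseline; 14 at week 2 and 12.5 at week 4 on placebo; SHG lower by 1 and 2 points; SD 4; correlation 0.6; the poorest responders (with some noise) lose week 4; trend fitted over patients; ANCOVA on baseline; 600 simulated trials per row. True difference -2.0.

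| Missing, SHG / placebo | Trend | LOCF | No imputation |
|---|---|---|---|
| 10% / 10% | -1.82 | -1.92 | -2.03 |
| 20% / 20% | -1.60 | -1.79 | -1.99 |
| 10% / 30% | -1.21 | -1.94 | -1.21 |
| 30% / 10% | -1.95 | -1.68 | -2.79 |

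Check against step 3: 0.9 x (-2.03) = -1.83 and 0.8 x (-1.99) = -1.59, against simulated -1.82 and -1.60.

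With equal loss, trend and LOCF shrink the effect, while the analysis without imputation happens to stay close to -2.0. With unequal loss, the last overstates or understates according to which arm loses more. No method is safe in every row.

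**The case against.** The strongest reply is that 2.4.5 itself provides for collecting data from patients who discontinue or deviate, and that the natural reading is collection despite withdrawal. That stands in part. A reader might infer that the rule necessarily produces missing week-4 ISI, and the document does not support this: it is a risk created by unclear wording.

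A reader might also infer that 2.11 discards values observed after discontinuation. It does not. It fills missing values only, and completing follow-up is required only for the per-protocol set.

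Nor does rescue lead automatically to withdrawal, since 2.7.2 keeps the patient under observation. This is right, and it is why the conflict lies between the two sections and not in 2.4.5 alone.

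Some of the lost values may not be obtainable. Criterion (1) applies to patients unable to continue, and the first limb of criterion (3) to patients who cannot follow the trial's procedures. This stands too, and imputation remains necessary for them.

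Finally, an article condenses, and the full protocol (version 2.0) may list the visits kept after discontinuation. That could settle the visit question. It does not remove the disagreement between two rules that the article does state.

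**Conclusion.** The point holds as an unresolved inconsistency with a real risk to the primary analysis. Section 2.4.5 withdraws patients from the trial for non-compliance or interfering medication and leaves later ISI collection undefined. Section 2.7.2 may keep the same patients, and one of its triggers is the primary outcome. If the stricter reading is followed, missing week-4 values are outcome-related, and neither the planned imputation nor the sensitivity analysis without it can be relied on to correct that.

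The size and direction cannot be fixed from the documents. One might multiply an arm difference in withdrawal by an error in the filled ISI, but the article gives neither. The pilot's 4.42 points (section 1) is a mean 2-week reduction, not an imputation error, and such a product is zero under equal withdrawal, where the illustration shows shrinkage to -1.60. The illustration shows only that the effect could matter if many patients were lost. It does not predict the bias in this trial, and the 32 patients allowed for loss cannot be attributed to this rule.

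**What to change.** Reconcile sections 2.4.5, 2.7.2 and 2.11, leaving the stopping and rescue rules themselves to the investigators. On data collection and analysis, state that:

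1. unless the patient withdraws consent to follow-up, the scheduled ISI assessments, at least week 4, continue whatever the treatment status or added medication;
2. values so observed enter the ITT analysis as observed;
3. imputation is used only for values truly not obtained.

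The cost is a short amendment with ethics committee agreement, plus the effort of keeping patients in visits that are already on the schedule. The statistical price is that off-treatment or post-rescue values may dilute the effect slightly.
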